### Outcome measures

Primary outcomes include the Norwich Patellar Instability Scale [13] collected at the time of enrollment, 4 weeks, 9 weeks, 6 months, and 12 months after enrollment, isometric and isokinetic quadriceps strength at 1 week, 4 weeks, 9 weeks, 6 months, and 12 months after enrollment, MRI T1ρ and T2 relaxation times 1 week, and 12 months enrollment, and biochemical biomarkers which will include urinary C-terminal cross-linked telopeptide type II collagen (CTXII) and a neoepitope of type I and type II collagen cleavage (C1,2C) at the time of enrollment, 4 weeks, 9 weeks, 6 months, and 12 months after enrollment. Secondary outcomes include the VAS for pain [14], Cincinnati Occupational Rating Scale [15], Tegner Activity Scale [16], and the time to returning to work and/or sporting activities, hip muscle strength (hip abduction, hip external rotation), and knee biomechanics (knee extensor moment, knee flexion excursion, knee adduction moment, knee adduction excursion) during walking, running, and anterior step-downs 1 week, 9 weeks, 6 months, and 12 months after enrollment. Data will be captured using REDCap and will be reviewed on a quarterly basis by an unblinded member of the study team to ensure data quality and completeness (Table 2).

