### Statistical methods

The primary outcome variable for Aim 1 is the Norwich Patellar Instability Scale. Utilizing the standard deviation of 18.6 points from our pilot results, a sample size of 34 subjects per group will be adequately powered (80%) to detect a moderate effect size between groups difference (13 points difference, effect size = 0.7). To protect against up to 15% of subjects being lost to follow-up, an additional 5 subjects will be enrolled per group (39 subjects per group; 78 total). Based on our previous pilot work, a sample size of 34 patients per group will also be more than 80% powered to detect group differences in the primary outcome variables for both Aim 2 (quadriceps strength and knee biomechanics) and Aim 3 (T1ρ relaxation time).

Since all endpoints are quantitative and longitudinal data is collected, repeated measures analysis of covariance (ANCOVAs) will be used to assess differences in scales across the two treatment groups (BFRT vs. sham BFRT). The repeated measures ANCOVAs will adjust for demographic covariates (e.g., age, sex, and race) as well as look for differences across any other potential confounders (such as first-time vs. repeated instability events). Assumptions such as normality and constant variance will be assessed, and remedial measures will be employed as needed. In addition, interaction effects and/or variable transformations will be explored appropriately. In the case that endpoints are related, multivariate analysis of covariance (MANCOVAs) may be used to consider those that naturally group themselves.

All analyses will be performed with a significance level of 0.05, and appropriate multiple comparisons adjustments will be performed as needed. Categorical variables will be described with counts and percentages and analyzed using appropriate statistical methods, such as hypothesis tests or logistic regression models.

For both primary and secondary analyses, in the case of participants that violate group allocation or do not attend a minimum of 80% of the prescribed physical therapy sessions, we will perform intention-to-treat and per protocol analyses. We will not employ imputation methods in the case of missing data. No interim or other subgroup analyses will be performed.

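### The enrolment value of the outcome is not named as a covariate, and its role in the repeated measures model is not stated

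*Protocol article*

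**What the plan says.** The Statistical methods section of the protocol article plans repeated measures ANCOVA for the longitudinal endpoints and describes the covariates: "The repeated measures ANCOVAs will adjust for demographic covariates (e.g., age, sex, and race". The same sentence adds that differences across other possible confounders will be looked for, with first versus repeated instability as the example. The enrolment value of the outcome is not mentioned.

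The Outcome measures section shows that this value will be available: "Norwich Patellar Instability Scale [13] collected at the time of enrollment, 4 weeks, 9 weeks, 6 months, and 12 months after enrollment". The two urinary or biochemical markers, CTXII and C1,2C, follow the same schedule. Quadriceps strength and MRI are first measured at 1 week, so this point does not cover them.

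The sample size rests on the Norwich score: "The primary outcome variable for Aim 1 is the Norwich Patellar Instability Scale". Its inputs are an SD of 18.6 points, a target of "13 points difference, effect size = 0.7", 34 evaluable patients per group and 80% power. With the allowance for loss this becomes "39 subjects per group; 78 total". The Randomization, group allocation, and blinding section stratifies by sex only.

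**The concern.** For a score measured before and after treatment, the patient's own starting value is a natural covariate to fix in advance. Here the stated set is demographic, and the starting value appears neither in it nor in the example given for other confounders.

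Patients may enter after a first or a recurrent dislocation and up to 3 months after the event, so varied enrolment scores are plausible. Nothing in the randomisation balances those scores. Two things are at stake:

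- **Precision.** Variation that the enrolment score could explain stays in the residual.
- **Chance imbalance.** If the groups happen to start apart, part of the gap passes into an unadjusted follow-up comparison.

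The word ANCOVA does not settle what happens to the enrolment measurement. It could be a covariate, the first of five responses, the base for a change score, or unused. These choices give different estimates and different power.

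**Working it through.** **Inputs from the article (Statistical methods).** Difference 13 points; SD 18.6; 34 per group; equal allocation; significance level 0.05. Sidedness is not stated and two-sided is assumed.

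**Inputs assumed.** The correlation r between enrolment and follow-up Norwich scores is 0.3, 0.5 or 0.7. The SD of 18.6 is taken to apply at enrolment and at follow-up. The article gives no correlation and does not say at which visit the pilot SD was measured.

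**Step 1: reproduce the plan's figure.** Effect size = 13/18.6 = 0.699. A two-sided two-sample t-test needs 33.1, so 34 per group, and has power 0.810 at 34. A one-sided test would need 26 (normal approximation). The stated size is therefore that of an unadjusted two-sided comparison and does not depend on baseline adjustment.

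**Step 2: one follow-up visit.** Power is for a two-sided t-test at 34 per group.

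- Adjusted for enrolment: residual SD = 18.6 × √(1 − r²), which is 17.7, 16.1 and 13.3. The variance reduction r² is 9%, 25% and 49%.
- Change from enrolment: SD = 18.6 × √(2(1 − r)), which is 22.0, 18.6 and 14.4.

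| Analysis | r = 0.3 | r = 0.5 | r = 0.7 |
|---|---|---|---|
| Follow-up value, unadjusted | 81% | 81% | 81% |
| Change from enrolment | 67% | 81% | 96% |
| Follow-up value, adjusted for enrolment | 85% | 91% | 98% |

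The half-width of the 95% confidence interval falls from 9.0 points unadjusted to 8.6, 7.8 and 6.4 points adjusted.

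**Step 3: several visits together.** This also assumes the same r between every pair of visits and a constant 13-point effect at all four later visits.

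- Group main effect over all five visits, enrolment included: the effect is diluted to 13 × 4/5 = 10.4 points, because enrolment carries no treatment effect. SD = 18.6 × √((1 + 4r)/5).
- Mean of the four later visits, unadjusted: SD = 18.6 × √((1 + 3r)/4), which is 12.8, 14.7 and 16.4.
- The same mean, adjusted for enrolment: SD = 18.6 × √((1 + 3r)/4 − r²), which is 11.5, 11.4 and 9.9.

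| Analysis | r = 0.3 | r = 0.5 | r = 0.7 |
|---|---|---|---|
| Main effect over five visits | 93% | 83% | 74% |
| Mean of four later visits, unadjusted | 98% | 95% | 90% |
| Mean of four later visits, adjusted | above 99% | above 99% | above 99% |

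**Step 4: chance imbalance.** The standard error of the enrolment difference between groups is 18.6 × √(2/34) = 4.5 points. In an unadjusted single-visit comparison, a gap of that size shifts the estimate by r × 4.5 = 1.4, 2.3 or 3.2 points. The two-sided 5% extreme is 1.96 × 4.51 = 8.8 points, which would carry over 2.7, 4.4 or 6.2 points.

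**The case against.** A reader might infer that the plan rules out baseline adjustment. It does not. The article is silent, other confounders are left open, and a condensed article may leave the exact model to an analysis plan that is not shown. This stands, so the point can only be that the enrolment value is not named.

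The silence is not wholly neutral, though. The article chose to state covariates, and the open-ended list is one of demographic variables, which a Norwich score is not. The remaining clause describes a look for differences across confounders rather than a fixed adjustment. A covariate that entered only after an imbalance was seen would make the primary model depend on the data.

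A repeated measures model may also carry enrolment as its first time point. If it fits a common enrolment mean for both groups, it is essentially equivalent to adjustment and nothing is lost. If it compares change, the imbalance is subtracted but power is lower than with the covariate; at r = 0.7 the gap is small, 96% against 98%. If it tests a main effect that includes enrolment, the effect is diluted. The article does not say which applies.

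A reader might further infer bias, an inflated type I error or an underpowered trial. None of these follows. Randomisation keeps the estimate unbiased on average and the test valid. The standard error already allows for chance imbalance, and the unadjusted comparison reaches 81%.

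Finally, the size of the gain rests on assumptions. At r = 0.2 the variance reduction is only 4%. The 8.8-point gap is an extreme case, so the one-standard-error figures are the fairer guide. The single-visit powers are not those of the full repeated measures model.

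**Conclusion.** The point holds as a forgone gain in efficiency and an unsettled modelling choice, not as an error in validity or planned power. The article does not name the enrolment value as a covariate and does not give the enrolment measurement a role.

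A model with only the named covariates forgoes precision and leaves chance imbalance in that trial's estimate. A change-score contrast, or a main effect that includes the enrolment visit, is also less efficient than the covariate at each correlation examined.

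On the assumed SD and correlations, single-visit power would go from 81% to 85–98%, and a 4.5-point enrolment gap would move an unadjusted estimate by 1.4 to 3.2 points. The direction of the gain is firm for any appreciable correlation; its size is not known from the article.

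**What to change.** For Norwich, CTXII and C1,2C, prespecify the patient's enrolment value as a fixed covariate in the repeated measures model, whatever imbalance is observed. Keep sex in the model, since it is the randomisation stratum. Analyse the 4-week, 9-week, 6-month and 12-month values as the responses, so that enrolment is not also a response.

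The cost is a line of analysis wording and one degree of freedom per model. The values are already scheduled for collection, and the sample size does not change. If the full analysis plan already does this, or fits a common enrolment mean, it is enough to say so in the protocol.

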## Methods/design

### Aims

The overarching rationale is that BFRT will expedite the return to work or sports, minimize muscle impairment, and ultimately slow cartilage degradation over the first year following patellar dislocation. This strategy will improve patient-reported outcomes and accelerate restoration of symmetric strength and knee biomechanics necessary to safely return to activity. We will test the following specific aims:

*AIM 1*: Determine if BFRT improves patient-reported outcomes and lessens the time to return to work or sport following patellar instability.

*Hypothesis:* BFRT will result in significantly improved responses on the patient-reported Norwich Patella Instability, visual analog scale (VAS) for Pain, Cincinnati Occupational Rating Scale, Tegner activity scores, and an earlier return to work and/or sport.

*AIM 2:* Assess whether BFRT results in more symmetric quadriceps strength and knee biomechanics following patellar instability.

*Hypothesis:* BFRT will result in improved quadriceps strength and knee biomechanics (knee moments and excursions).

*AIM 3:* Compare progressive changes in cartilage degradation, muscle architecture, and inflammatory profiles between those treated with or without BFRT over the first 2 years.

*Hypothesis:* BFRT will reduce degradative changes on Magnetic Resonance Imaging (MRI) as well as serum and urinary biomarkers of inflammation and cartilage degradation.

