### Randomization, group allocation, and blinding

Randomization: Following informed consent and after successfully being screened into the study based on exam findings, subjects will be randomized to one of two groups. The randomization schedule will be made a predesignated unblinded study team member that will not be involved in data collection or analysis. Using a random number generator, allocation of to either the BFRT or sham BFRT group will be by permutated random block size, ensuring that approximately equal numbers of subjects will be treated with drug or placebo in the unlikely event that the study will need to be terminated prematurely. Should a subject discontinue the study for any reason prior to the final follow-up visit, then the collected data will be evaluated but not included in the analysis and a replacement subject will be enrolled in the study. As such, the randomization schedule will be prepared for 100 potential participants despite having a target enrollment of 78 participants to ensure adequate power.

Blinding: The team member that prepared the randomization schedule will meet with the pre-specified unblinded study personnel prior to the site initiation visit. The unblinded personnel will then prepare sealed envelopes that contain each subject’s group assignment. All assessments and data analyses will be performed by a separate individual to the person applying the BFRT unit to ensure blinding. The study statistician will generate a randomization plan using SAS or R to assign subjects to groups. Randomization will occur by sex and be in sets of 2 subjects to ensure adequate distribution of all groups across the collection period. Patients will be randomized into one of the two following treatment groups:
Standard of care physical therapy + sham BFRTStandard of care physical therapy + BFRT

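### The MANCOVA option and the ban on imputation can drop patients who finish with one gap, and a MANCOVA p-value has no direction; a mixed model per endpoint is a cheap improvement

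*Protocol article*

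**What the plan says.** All of the analysis text is in Statistical methods in the protocol article.

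- **Main analysis:** "repeated measures analysis of covariance (ANCOVAs) will be used to assess differences in scales across the two treatment groups".
- **Multivariate option:** where endpoints are related, "multivariate analysis of covariance (MANCOVAs) may be used to consider those that naturally group themselves". The endpoints to be grouped and the weight of the result are not stated.
- **Missing data:** "We will not employ imputation methods in the case of missing data".
- **Error rate:** "All analyses will be performed with a significance level of 0.05, and appropriate multiple comparisons adjustments will be performed as needed".

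Two other sections bear on the point. For a subject who discontinues, Randomization, group allocation, and blinding says that "the collected data will be evaluated but not included in the analysis and a replacement subject will be enrolled in the study". In Aims, the hypotheses have a direction; for Aim 3 it is that "BFRT will reduce degradative changes on Magnetic Resonance Imaging (MRI) as well as serum and urinary biomarkers of inflammation and cartilage degradation".

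Outcome measures lists primary outcomes that form obvious pairs: isometric and isokinetic strength, T1ρ and T2, CTXII and C1,2C. The Norwich scale, strength and the biomarkers are each measured five times, the MRI measures twice.

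**The concern.** Two features of the stated method fit the trial poorly.

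**Complete vectors.** A standard MANCOVA needs every grouped value for a patient. A repeated measures ANCOVA has the same need if it is fitted as a classical general linear model. With imputation excluded, a patient who attends the last visit but lacks one earlier visit or one urine sample leaves the test altogether. This is separate from the rule on patients who discontinue, because these patients finish. It costs information, and it tilts the analysed set towards patients with perfect attendance.

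**No direction.** MANCOVA asks whether two mean vectors differ in any way. Two benefits, two harms of the same size, or one of each can all give a significant result. In a two-sided test on one endpoint the sign of the estimate settles the direction; the omnibus statistic has no sign. The Aims predict improvement, so a significant MANCOVA alone does not answer the question they ask.

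**Working it through.** **1. The plan's own figure.** Inputs from Statistical methods: difference 13 points, SD 18.6, power 80%, 34 per group, alpha 0.05 (taken as two-sided).
- Effect size: 13 / 18.6 = 0.699.
- The two-sample t test needs 33.1 per group, rounded up to 34; power at 34 is 81.0%.
- The stated sample size reproduces, and 34 per group is used below.

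**2. Loss from incomplete vectors.** Share complete = (1 − m)^k, for an assumed miss rate m at each of k occasions, independent between occasions. The article gives no m. For an endpoint with four visits after the first:
- m = 5%: 0.95^4 = 0.815, so 81% remain, or 34 × 0.815 ≈ 28 per group.
- m = 10%: 0.90^4 = 0.656, so 66% remain, or 34 × 0.656 ≈ 22 per group.
- If 39 finishers per group are kept through replacement: 39 × 0.815 = 31.8 and 39 × 0.656 = 25.6.

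At 31.8 and 25.6 per group, the two-endpoint test with 0.7 SD on both endpoints and correlation 0.5 has 81% and 71% power. If the only missingness is whole-patient dropout, there is no extra loss. T1ρ and T2 have a single later visit, so their loss is smaller.

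**3. Absence of direction.** Power of the two-group, two-endpoint test (Hotelling T²; MANCOVA without covariates) comes from the noncentral F with 2 and 65 degrees of freedom and noncentrality λ = (n/2) · δ′R⁻¹δ. For equal effects δ the quadratic form is 2δ²/(1 + r); for opposite effects it is 2δ²/(1 − r). With n = 34 and assumed r = 0.5:
- +0.35/+0.35 SD: λ = 17 × 0.1633 = 2.78, power 29%.
- +0.35/−0.35 SD: λ = 17 × 0.49 = 8.33, power 71%.
- +0.5/+0.5 SD: λ = 17 × 0.3333 = 5.67, power 54%.
- +0.5/−0.5 SD: λ = 17 × 1.0 = 17.0, power 96%.

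For 0.35 SD, as r goes from 0.3 to 0.7, power falls from 33% to 26% for concordant effects and rises from 56% to 91% for opposite effects. Changing both signs leaves λ unchanged, so two harms give the same power as two benefits.

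**4. Comparison with other tests for two concordant benefits.** The average of two standardised endpoints has effect size δ / √((1 + r)/2). At r = 0.5 the divisor is √0.75 = 0.866, so 0.35, 0.5 and 0.7 become 0.404, 0.577 and 0.808.

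| Benefit on both | MANCOVA | One endpoint, t test | Sign-aligned average |
|---|---|---|---|
| 0.35 SD | 29% | 30% | 38% |
| 0.5 SD | 54% | 53% | 65% |
| 0.7 SD | 84% | 81% | 91% |

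MANCOVA matches a single-endpoint test and trails the directional average. At 0.7 SD it gives 89% at r = 0.3 and 79% at r = 0.7, against 81% for one endpoint.

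**The case against.** The strongest reply is that MANCOVA is only an option. Endpoint-wise repeated measures ANCOVA is the stated main analysis, and it shows the direction of each effect. The Aim 1 primary variable is one scale and needs no multivariate test. Groupings and follow-up rules for an optional test are details that an article may leave to an analysis plan. This stands. A reader might infer that an Aim could be declared met on a MANCOVA p-value; the article contains no such rule. Loose wording leaves the possibility open, and no more than that.

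A reader might also infer that MANCOVA costs power in general. The figures do not support that: it is level with a single-endpoint test at correlation 0.5, better at 0.3 and slightly worse at 0.7. If alpha were split over two endpoints, each separate test would have only 20% at 0.35 SD and 41% at 0.5 SD.

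Nor is the loss of incomplete patients peculiar to MANCOVA or certain to happen. The article does not say how the repeated measures ANCOVA will be fitted, and excluding imputation is compatible with a likelihood fit that uses every observed visit. The miss rates above are assumed. With 39 finishers per group and 5% scattered misses, power stays near the planned 80%.

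The reply does not remove two facts: the named multivariate method, run as standard, discards finishers with one gap, and its p-value carries no sign.

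**Conclusion.** The point holds as a cheap improvement, not as an error that invalidates the analysis. MANCOVA, or a classically fitted repeated measures ANCOVA, loses any finisher with one missing value when imputation is excluded. The size of that loss cannot be fixed from the article: 81% or 66% complete is an illustration that rests on assumed, independent misses of 5% or 10% at four visits, and the extra loss is nil if only whole patients drop out.

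The omnibus test also does not match directional hypotheses. Against a sign-aligned average it gives up about 7 to 11 percentage points of power for two equal benefits of 0.35 to 0.7 SD, with 34 per group, two endpoints and correlation 0.5. Only the 0.7 effect size and the group size come from the article; the correlation and the smaller effects are assumptions.

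**What to change.** Make three changes to Statistical methods.

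1. Analyse each primary endpoint with a likelihood-based mixed model for repeated measures (treatment, visit, treatment by visit, unstructured covariance). It uses all observed visits and respects the exclusion of imputation.
2. State that any MANCOVA is supportive only, and that a significant result is not evidence of benefit unless the endpoint-wise results agree in direction.
3. If a joint claim is wanted, name the pair in advance and test the average of the two standardised endpoints, with signs aligned so that higher is better.

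The cost is a few sentences and a different procedure in the same software, with no new data or patients. There is a small downside: the mixed model relies on data being missing at random, and the omnibus test is given up as a basis for claims.

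### Repeated measures ANCOVA with imputation ruled out, read in its standard form, drops patients who finish the trial but miss a middle visit, so the stated 80% power is not assured

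*Protocol article*

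**What the plan says.** All of this is in the protocol article.

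- **Model (Statistical methods).** For the longitudinal endpoints, "repeated measures analysis of covariance (ANCOVAs) will be used to assess differences in scales across the two treatment groups". MANCOVA may be used where endpoints are related. No fitting method or covariance structure is given.
- **Missing data (Statistical methods).** "We will not employ imputation methods in the case of missing data".
- **Assumptions (Statistical methods).** "Assumptions such as normality and constant variance will be assessed, and remedial measures will be employed as needed". Correlation between visits is not mentioned.
- **Visits (Outcome measures).** The Norwich scale is "collected at the time of enrollment, 4 weeks, 9 weeks, 6 months, and 12 months after enrollment". Quadriceps strength and the biochemical markers also have five time points. T1ρ and T2 are measured only at 1 week and 12 months.
- **Sample size (Statistical methods).** "Utilizing the standard deviation of 18.6 points from our pilot results" and a target of "13 points difference, effect size = 0.7", the plan takes 34 per group for 80% power. It adds 5 per group against up to 15% loss to follow-up, giving 39 per group and 78 in total.
- **Discontinuation (Randomization, group allocation, and blinding).** Patients who stop before the final visit are left out of the analysis and replaced, from a schedule prepared for 100.

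**The concern.** Classical repeated measures ANCOVA and MANCOVA work on a complete set of values per patient. With imputation excluded, one gap at a middle visit removes the whole patient, including an observed 12-month value. This affects patients who finish the trial, so it is a different problem from the rule on discontinuers. Those removed are also selected by attendance.

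The sample size makes no provision for it: the 5 extra patients per group are set against loss to follow-up, and replacement is triggered only by discontinuation.

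A second issue concerns the error rate. The univariate within-subject tests of the classical method assume sphericity, and correlation that decays across visits from 0 to 52 weeks breaks it. The Abstract and Aims hypothesise faster recovery, and a group-by-visit test is a natural way to examine that. Uncorrected, this test would reject too often.

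**Working it through.** **Inputs from the protocol:** difference 13, SD 18.6, 34 per group (39 with the allowance), and "All analyses will be performed with a significance level of 0.05". Sidedness is not stated; two-sided is assumed.

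**Assumed:** a miss rate *m* per middle visit, independent across the three middle visits (4 weeks, 9 weeks, 6 months) and equal in both arms.

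**Step 1. Reproduce the plan's figure.** d = 13/18.6 = 0.699. A two-sample t-test at two-sided 0.05 needs 33.1 per group for 80% power, so 34. Power at 34 per group is 81.0%, and at 39 per group 86.2%. The plan's 34 is confirmed.

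**Step 2. Power after complete-case loss.** The fraction of completers with all three middle visits is (1 − m)³: 0.97³ = 0.913, 0.95³ = 0.857, 0.90³ = 0.729. Multiply by the completers per arm and recompute the t-test power at d = 0.699.

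| Missed per middle visit | From 34 completers per arm | Power | From 39 completers per arm | Power |
|---|---|---|---|---|
| 3% | 31.0 | 77% | 35.6 | 83% |
| 5% | 29.2 | 75% | 33.4 | 80% |
| 10% | 24.8 | 67% | 28.4 | 74% |

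The 34 column applies if the whole allowance is spent on drop-out. The 39 column applies if replacement works in full.

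**Step 3. Where 80% is lost.** Solve n(1 − m)³ = 33.1. From 34 completers, m = 1 − (33.1/34)^(1/3), about 0.9%. From 39, m = 1 − (33.1/39)^(1/3), about 5.3%.

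**Step 4. Dependence on the contrast.** Steps 2 and 3 use the plan's own basis, a simple two-group comparison. If the 13-point effect is the same at every modelled visit and the visits are averaged, the group main effect has 89% to 98% power at 34 per arm under the assumed decaying correlations, and needs only about 16 to 26 per arm for 80%. The protocol does not fix the contrast.

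**Step 5. Type I error.** Null data were simulated with 34 per arm, 6,000 runs per setting, with correlation decaying over weeks 4/9/26/52 or 0/4/9/26/52. Sphericity epsilon ranged from about 0.51 to 0.77.

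- Group main effect: 0.046 to 0.051.
- Group-by-visit, uncorrected: 0.067 to 0.088. A second set of runs, with covariance 0.3 + 0.7ρ^(weeks/4) and ρ of 0.9, 0.8 and 0.7, gave 0.089, 0.073 and 0.063.
- Group-by-visit with Greenhouse-Geisser correction: 0.045 to 0.053.

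Under equal correlation of 0.5 (epsilon 1) the uncorrected test ran at 0.050 to 0.051 on the same unequally spaced visits. The decay of correlation therefore causes the inflation, and unequal spacing alone does not.

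**Step 6. Scope.** An outcome with one baseline and one follow-up value has no middle visit to miss, and sphericity holds trivially with two time points. T1ρ and T2 are therefore outside this point.

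**The case against.** The strongest reply is that deletion of incomplete patients is inferred. The protocol never says it, a repeated measures ANCOVA can be fitted by likelihood, and such a fit uses partial data without imputing anything. Details of estimation often sit in an analysis plan, which is not shown here. This stands to the extent that the text does not exclude a likelihood fit. But the protocol names the classical method with MANCOVA as its companion, mentions no mixed model, and elsewhere sets aside the partial data of discontinuers. The complete-data reading is the natural one.

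A reader might go further and infer that the 80% power and the 0.05 level are simply not delivered. The documents do not support that:

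- **Power.** No miss rate is given. With full replacement, 80% survives up to about 5% missed per visit, and a constant effect averaged over visits has power to spare.
- **Error level.** The comparison that the plan names is between treatment groups, and non-sphericity leaves that test near 0.05. Interactions are only to be explored. The list of assumptions is open-ended, and a Greenhouse-Geisser correction would count as one of the remedial measures it promises.

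**Conclusion.** The point holds in a limited form. As written, the method and the no-imputation rule together leave the 80% power unassured for outcomes with several follow-up visits, because nothing in the sample size or the replacement rule protects against single missed visits. At the assumed miss rates of 3% to 10%, power on the plan's own basis lies between 67% and 77% from 34 completers per arm and between 74% and 83% from 39. These figures rest on complete-case deletion, independent misses and a single two-group contrast.

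The inflation to about 0.06 to 0.09 is confined to an uncorrected group-by-visit test under decaying correlation.

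This should be changed, because a better analysis costs almost nothing. If a likelihood fit was already intended, one sentence settles the matter.

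**What to change.** For outcomes with more than one follow-up visit, state that the analysis is a mixed model for repeated measures fitted by REML, with categorical visit, treatment-by-visit terms and unstructured covariance, plus a simpler structure named in advance in case the model does not converge. State that it uses all available follow-up values of every patient in the analysis set. Completers with a gap then stay in. The unstructured covariance removes the reliance on sphericity, and the no-imputation sentence can stand.

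Who belongs in the analysis set is a separate question. The exclusion of discontinuers and of inadvertently unblinded patients (Randomization, group allocation, and blinding) has to be reconciled with the intention-to-treat analysis named in Statistical methods. The wording above does not settle that.

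The cost is a change of analysis wording and a few more covariance parameters to estimate. No extra patients or visits are needed.
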